### Inclusion criteria

- Age >35 years
- Current / former smoker & smoking burden >10 pack years
- Clinical diagnosis of COPD, supported by previous obstructive spirometry
- Admission to hospital with the primary cause being an exacerbation of COPD

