## Study Design and Methods

### Methods

A randomised (1:1) pilot study of 120 consecutive consenting patients. The intervention group will undergo a comprehensive cardiac assessment and standardised treatment protocols will be followed to treat identified CVD. Patients will be followed for 12 months to gather outcome data. CVD is defined as hypertension, ischaemic heart disease (IHD), HFPEF, HFREF, atrial or ventricular arrhythmia, moderate-severe valvular heart disease or cor pulmonale.

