| SGRQ-C                                           | X | X |   |   | X |
| EQ-5D-5L                                         | X | X |   |   | X |
| Exacerbation frequency                           | X | X | X | X | X |
| Hospital admissions / ED attendances             |   | X |   |   | X |
| Primary & community NHS care visits π |   | X | X | X | X |
| Mortality                                        |   |   |   |   | X |
| Adverse Cardiovascular Events ‡                  |   | X |   |   | X |

† - at clinical stability, defined as > 6 weeks after completion of primary treatment course for COPD exacerbation; \* - includes; BMI, previous spirometry, previous exacerbation / hospital admission / NIV episodes, α- components of NEWS2 scale; π – health service utilisation form; β – full blood count, urea & electrolytes, liver function tests, glucose, albumin, lactate, CRP; ‡ nonfatal stroke or myocardial infarction, and cardiovascular death

In addition to face to face assessments, all patients will be contacted by telephone at 6 and 9 months to complete an assessment of healthcare resource use. In hospital and at 3, 6 and 9 months following hospital discharge, patients will be provided with a health service utilisation form and asked to use this to record all contact with community NHS services. This data will be reviewed with the patient at the face to face (3 and 12 months) and telephone (6 and 9 months) assessments. Data regarding frequency of COPD exacerbations will be collected at these time points; severe exacerbations (requiring admission) will be captured from health records, moderate exacerbations (requiring treatment with antibiotics and/or steroids) will be self-reported.

Clinical stability is required at the 90-day review for accurate assessment of spirometry and, for those randomised to structured cardiovascular assessment, for echocardiography. The 90-day review appointment will therefore be delayed, if necessary, until participants are in a period of clinical stability, which is defined as more than 4 weeks after completion of a course of steroids and/or antibiotics for a diagnosed COPD exacerbation. The research fellow may clinically assess participants to determine if a COPD exacerbation should be diagnosed if a patient is unwell around the time of review. To avoid excessive delay in cases

of recurrent exacerbation, 90 day review will be conducted after the delay has reached 8 weeks, regardless of the recency of exacerbation.

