### Secondary

1. Time to readmission or death following hospital admission for ECOPD
2. All-cause readmission rates at 90 days and 12 months post discharge
3. All-cause mortality rates at 90 days and 12 months post discharge
4. COPD exacerbation rates, from health records and self-reported, at 90 days and 12 months.
5. Rates of adverse cardiovascular events\* at 90 days and 12 months post discharge
6. Rate of new diagnosis of cardiovascular disease at 90 days and 12 months
7. Rate of undertreated cardiovascular disease at baseline, 90 days and 12 months
8. Change in 4 metre gait speed at 90 days and 12 months, compared to baseline
9. Mean change in quality of life measured by St. Georges' Respiratory Questionnaire over 12 months.
10. Health costs and estimated Quality Adjusted Life Years (QALY), measured by health records and patient-completed resource utilisation proforma, at 12 months

In the intervention arm we will also report as secondary outcomes:

11. Changes in right heart function† between baseline and 90 days
12. Relationship between changes in right heart function† and ECOPD severity measured using DECAF score
13. Relationship between changes in right heart function† and comorbid CVD
14. Relationship between right heart function† and COPD severity at baseline.
15. The associations between the primary outcome and right heart function at baselinet.

\* nonfatal stroke or myocardial infarction, and cardiovascular death; † Estimated pulmonary artery systolic pressure (PASP) and tricuspid annular plane systolic excursion (TAPSE) measured by echocardiography.

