### Randomisation

Patients will be randomly assigned 1:1 to the intervention or usual care. Independent stratified randomisation (via sealedenvelopes.com) using the PEARL score [25] (low, medium and high risk) and the presence of known CVD pre-hospital admission will be performed.

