### Outcome measurements

Changes in the primary outcome between the intervention and usual care groups will be assessed using Student's t-test or Mann-Whitney U test. Time to first event (readmission or death) will be assessed using a Cox proportional hazards regression model. Changes in echocardiographic measurements between two time points will be assessed using paired Student's t-test or Wilcoxon signed-rank test. The relationship between undiagnosed / undertreated cardiac disease and outcome will be examined using logistic regression. In those surviving to the first follow up assessment, correlations between changes in right heart function and measures of COPD severity and exacerbation severity will be examined using bivariate comparisons appropriate to variable distribution. Mean change in QoL will be calculated by area under the curve per unit time; Student's t-test or Mann Whitney U will be used to compare this value between study arms.

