### Economic evaluation

The methods to estimate an incremental cost-effectiveness ratio for the intervention versus usual care in terms of Quality Adjusted Life Years will be rehearsed (using EQ-5D-5L administered at baseline, 90 weeks and 12 months post discharge). In particular, issues relevant for sensitivity analysis will be explored to help understand how best to deal with statistical imprecision and other uncertainties in the full trial. For example, data will be bootstrapped to account for the expected skewness evident in economic cost data. The data collected as part of this feasibility study could be used to inform any subsequent pre-trial modelling.

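### The SGRQ comparison is fixed as an unadjusted t-test or Mann-Whitney U test, giving up precision that the baseline SGRQ-C and the stratification factors could supply at almost no cost

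*Protocol*

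**What the plan says.** Secondary outcome 9 is "Mean change in quality of life measured by St. Georges' Respiratory Questionnaire over 12 months". The Schedule of Activities collects SGRQ-C at baseline, 90 days and 12 months. Outcome measurements fixes the summary and the test: "Mean change in QoL will be calculated by area under the curve per unit time; Student's t-test or Mann Whitney U will be used". It names no covariate, and does not say whether the baseline score is subtracted from the area under the curve.

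Patients enter through "Admission to hospital with the primary cause being an exacerbation of COPD". The baseline column also holds blood gases and NEWS2 components, so baseline belongs to the acute admission. For the next visit, "Clinical stability is required at the 90-day review for accurate assessment of spirometry". That visit may be postponed, but goes ahead once the delay reaches 8 weeks. No stability rule is attached to the 12-month visit.

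The Methods section describes "A randomised (1:1) pilot study of 120 consecutive consenting patients". Randomisation is stratified "using the PEARL score [25] (low, medium and high risk) and the presence of known CVD pre-hospital admission will be performed".

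**The concern.** A change score carries the whole of the baseline variance. When baseline and follow-up are only moderately correlated, subtracting the baseline adds more noise than it removes, and regression on baseline does better. This design invites that situation, because baseline is taken in an exacerbation and the 90-day score is meant to be taken near stability. A chance difference between arms in acute baseline status also passes straight into an unadjusted comparison of change.

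The result has uses beyond its place in the list. A secondary objective judges the novel primary outcome against quality of life, and the Study Endpoints section says the secondary outcomes help to power the definitive trial. A Mann-Whitney p-value alone gives no difference in SGRQ points to plan from.

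The scaling per unit time raises a matter of interpretation. A patient who dies after the 90-day review counts the same as one followed for a year, and a patient who dies before it has no follow-up score. The result describes quality of life while alive and must be read beside the deaths.

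**Working it through.** The protocol states no SD, correlation or target effect for SGRQ, so there is no figure to reproduce. The check compares the variance of the unadjusted summary with its variance after regression on baseline.

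**Inputs from the protocol:** visits at days 0, 90 and 365; 60 patients per arm.

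**Assumed:** follow-up SD 1; baseline SD k (k = 1 first); correlation r between baseline and each follow-up, 0.3 to 0.7; correlation q between follow-ups, 0.7 to 0.8; complete data; baseline subtracted from the area.

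**Weights.** The trapezoid rule over one year gives 90/365/2 = 0.123 for baseline, 0.500 for day 90 and (1 − 90/365)/2 = 0.377 for day 365. So change = −0.877·Y0 + 0.500·Y1 + 0.377·Y2, and 0.877² = 0.769.

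**Variances.** Let V = 0.500² + 0.377² + 2·0.500·0.377·q, which is 0.656 at q = 0.7 and 0.693 at q = 0.8.

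- Unadjusted: 0.769·k² + V − 2·0.769·k·r
- Adjusted for baseline: V − 0.769·r²
- Difference: 0.769·(k − r)²

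With k = 1 (unrounded weights):

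| r | q | Unadjusted | Adjusted | Ratio | Variance cut | SE cut | Unadjusted N matching 120 adjusted |
|---|---|---|---|---|---|---|---|
| 0.3 | 0.7 | 0.963 | 0.586 | 0.61 | 39% | 22% | 197 |
| 0.5 | 0.7 | 0.656 | 0.463 | 0.71 | 29% | 16% | 170 |
| 0.7 | 0.7 | 0.348 | 0.279 | 0.80 | 20% | 10% | 150 |
| 0.7 | 0.8 | 0.386 | 0.317 | 0.82 | 18% | 9% | 146 |

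The SE cut is 1 − √ratio and the last column is 120/ratio.

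**Cost of estimation.** One baseline covariate inflates the adjusted variance by 1 + 1/(120 − 4) = 1.009. With it, the unadjusted-to-adjusted ratios at q = 0.7 are 1.63, 1.40 and 1.24 for r = 0.3, 0.5 and 0.7. A simulation of 4000 trials gave 1.67, 1.42 and 1.23. At r = 0.5 the difference detectable with 80% power (two-sided 0.05) falls from 0.414 to 0.350 SD. An effect with 80% power unadjusted has about 91% adjusted.

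**Unequal SDs.** Here r runs from 0.2 to 0.8, with q = 0.7 (0.8 when r = 0.8). With k = 1.2 the unadjusted-to-adjusted ratio is 1.60 to 2.21. With k = 0.8 it is 0.99 to 1.43. The difference formula shows why: at k = r = 0.8 it is zero, and the lost degree of freedom leaves a 1% loss.

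**No baseline subtraction.** If the text means the raw area per unit time, the ratio with k = 1 is 1.13 (r = 0.2) to 4.34 (r = 0.8). Adjustment helps on that reading too.

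**Chance imbalance.** One standard error of the baseline difference is √(2/60) = 0.18 SD. It shifts the unadjusted change by 0.877·(1 − r)·0.18, which is about 0.11 SD at r = 0.3 and 0.05 SD at r = 0.7.

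**The case against.** The strongest reply is that this is one secondary outcome in a pilot, that randomisation keeps the unadjusted test valid, and that the SDs and correlations for the definitive trial can be estimated from the data whichever test is used. All of that is true. It limits the consequence to precision and does not defend the choice of test.

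The size also rests on assumed values, and with a narrow baseline spread and a high correlation there is no gain. That stands. Stratification by PEARL, which contains a dyspnoea score, will limit some baseline imbalance. That stands too, but it does not balance SGRQ itself.

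Three stronger readings are tempting and are not supported:

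- A reader might infer that all follow-up is taken in a stable state. The stability rule covers the 90-day visit only and lapses after 8 weeks' delay. It is justified by spirometry and echocardiography, not by quality of life. The 12-month score, with weight 0.377, has no such rule.
- A reader might infer the same error for gait speed and QALYs. The endpoint "Change in 4 metre gait speed at 90 days and 12 months, compared to baseline" defines a measure and names no test. The Economic evaluation section, "using EQ-5D-5L administered at baseline, 90 weeks and 12 months post discharge", describes methods to be rehearsed, and a QALY is not a change score. Covariates there may be left to the analysis plan.
- A reader might infer that the unadjusted comparison is biased, or that patients should be weighted by follow-up time. The first does not follow under randomisation. The second would use a post-randomisation weight that depends on death, which the intervention may affect.

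**Conclusion.** The point holds as one of efficiency. The protocol itself names a test that cannot use the baseline SGRQ-C or the stratification factors, so this is not detail left to a later document. With equal SDs, baseline subtraction and the correlations assumed above, adjusting for baseline is worth about 18 to 39% of the variance. The range is wider once the SD ratio and the unclear definition of the summary are allowed for, and it includes no gain in one corner. That baseline correlates only modestly with follow-up is an inference from the design, not a figure in the protocol. The loss is of precision on a secondary outcome. The primary outcome is untouched. The change should be made because it costs so little.

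**What to change.** In Outcome measurements, replace the t-test or Mann-Whitney U for quality of life with a linear regression of the SGRQ-C area-under-the-curve summary on arm, baseline SGRQ-C, PEARL category and known cardiovascular disease. Report the adjusted difference in SGRQ points with a 95% confidence interval, bootstrapped if the residuals are skewed. State whether baseline is subtracted from the area; once baseline is in the model, the two versions give the same arm difference when every patient has the same visit times. Label the result as while alive and show it beside deaths by arm. Do not weight by follow-up time.

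The cost is a change of wording and four degrees of freedom: one for baseline SGRQ-C, two for PEARL and one for cardiovascular disease. All the data are already collected. Even if the last three explained nothing and were not balanced by design, the same formula gives an inflation of 1 + 4/(120 − 7) = 1.035, small against most of the range above.

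Baseline adjustment of gait speed and QALYs is an optional parallel step, since the protocol fixes no test for them.

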### Economic evaluation

The methods to estimate an incremental cost-effectiveness ratio for the intervention versus usual care in terms of Quality Adjusted Life Years will be rehearsed (using EQ-5D-5L administered at baseline, 90 weeks and 12 months post discharge). In particular, issues relevant for sensitivity analysis will be explored to help understand how best to deal with statistical imprecision and other uncertainties in the full trial. For example, data will be bootstrapped to account for the expected skewness evident in economic cost data. The data collected as part of this feasibility study could be used to inform any subsequent pre-trial modelling.

## Power calculation

This is a pilot study. The lack of published data regarding both the prevalence of undiagnosed cardiovascular disease in patients hospitalised with ECOPD, and the impact of cardiovascular assessment (and treatment) on our primary outcome means a power calculation is not possible. We have previously successfully recruited 118 patients hospitalised with mild ECOPD over 18 months to a RCT of hospital at home in ECOPD. This recruited from a smaller population than the present proposal (~50% of total population) and involved a complex intervention.

Readmission and mortality rates are high following ECOPD; based on our pilot data, we are optimistic that our chosen sample size will be deliverable and show a treatment effect that will enable a definitive trial to be powered.

## Limitations

This study examines the effect of a novel intervention on a novel COPD outcome. The aim is to use the results to power a definitive RCT, but a lack of a treatment effect may mean a definitive trial is superfluous. Adequate echocardiographic images to make reliable measurements can be challenging in patients with COPD, particularly during an exacerbation when they are more breathless. Whilst a reduction in the amount of echocardiographic data available may reduce the ability to diagnose patients with HFpEF, HFrEF or valvular heart disease, this information will be vital in order to adequately power a definitive trial.

## Section S2: Management summaries

### SCATECOPD Management summary: heart failure

#### Definitions

*The following practical definitions reflect implementation of evidence and international guidelines by local cardiology services:*

1. Heart failure with moderate-severe LV systolic impairment
  - LVEF < 45% at transthoracic echocardiography (echo)
2. Heart failure without moderate-severe LV systolic impairment
  - LVEF ≥ 45% with echo report of LV diastolic dysfunction
3. Right sided heart failure:
  - Echo evidence of RV impairment in patient with peripheral oedema

*Echo should be performed as early as possible during admission. If NIV used, wait until weaned to periods of ≥ 4 hours off NIV*

### Treatment goals

1. In patients with moderate-severe LV impairment, establishment of maximum tolerated dose of beta blocker and ACE-inhibitor, +/- spironolactone, with referral to heart failure team for supervision of this
2. In all other patients with heart failure, euvolaemia and control of hypertension, AF and CAD if present

### Acting on echo reports

1. In patients with moderate-severe LV systolic impairment refer to heart failure service for ongoing supervision of the below:
  - a) Start bisoprolol 1.25mg provided heart rate (HR) above 65 bpm and ECG excludes 2nd/3rd degree AV block
    - If already on bisoprolol increase dose if HR > 65 bpm
    - If on carvedilol, this can be continued/increased depending on HR
    - If on a different beta blocker, switch to bisoprolol at equivalent dose***Titrate beta blocker dose every 2 weeks initially, aiming for HR < 70 bpm***
  - b) At the same time, introduce ramipril 1.25mg OD provided not hypotensive or hyperkalaemic, or on ARB
    - If cough/other insensitivity to ACE-inhibitor, introduce losartan 12.5mg OD***Titrate ACE-inhibitor/ARB dose every 2 weeks initially, aiming for normal BP and stable creatinine***
  - c) If clinically hypervolaemic and not on diuretics, introduce furosemide 40mg OD
    - If already on furosemide increase dose by 40mg/d
  - d) When beta blocker and ACE inhibitor doses stabilised, introduce spironolactone 25mg OD if LVEF < 35%.
2. For all other patients with heart failure:  
***If admission CXR shows pulmonary congestion/oedema but LVEF >45%, review echo and clinical presentation with cardiologist to determine if treatment as for patients with moderate-severe LV systolic impairment is recommended***
  - b) If clinically hypervolaemic and not on diuretics, start furosemide 40mg OD
    - If already on furosemide increased dose by 40mg/d up to maximum 360mg/d
  - c) Address hypertension, AF, diabetes and CAD if present (see relevant recommendations)
3. If echo is of poor quality and LVEF cannot be accurately quantified, arrange contrast echo as inpatient

### Specialist referral criteria

- Patients with echo report of heart failure with moderate to severe valve disease should be discussed with a cardiologist prior to initiation of new medications (see protocol for management of valve disease)
- Patients who have been established on maximally tolerated doses of beta blocker, ACE-I and spironolactone and remain symptomatic should be referred to cardiology for further specialist input (this should happen via the heart failure service)

### SCATECOPD management summary: lipids and coronary artery disease

#### Rationale and definitions

- Statins are likely to be required in a high percentage of patients in the SCATECOPD study, either because of known coronary artery disease (CAD) or because of high risk of future CAD-related events
- Known CAD is defined as previous myocardial infarction (MI) or coronary revascularisation
- CT calcium score ranges between 0 and 1000+
  - Scores  $\geq 100$  are regarded as moderate to severe and have been demonstrated to correlate with significant coronary artery stenosis and a risk benefit-ratio favouring primary prevention with aspirin

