#### QRISK3

- Gives the likelihood of a patient without established cardiovascular disease developing it within the next 10 years
- **Calculate for all patients** at <https://www.qrisk.org/three/index.php> using admission HDL/total cholesterol level
  - If total cholesterol  $> 7.5$  mmol/l or non-HDL cholesterol  $> 5.9$  mmol/l QRISK3 should not be used; repeat fasting lipid profile and assess for familial hypercholesterolaemia using FATS7 strategy (see reference)

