#### Treatment with statins

*Switch any existing statin prescriptions to those recommended below. Before starting, check ALT is not  $> 3 \times$  upper limit of normal and there is no unexplained muscle pain (see FATS7)*

- ***Patients with known CAD should be taking atorvastatin 80mg OD***
- ***Patients without the above, but who have QRISK3  $\geq 10\%$  should be taking atorvastatin 20mg OD***

- Additionally, patients over 40 with type 1 diabetes, or with CKD at any age (defined as albuminuria or eGFR <60ml/min/1.73m^2), should be offered atorvastatin 20mg OD regardless of QRISK3 score
- *Patients with QRISK3 < 10% but with CT calcium score ≥ 1 should be taking atorvastatin 20mg OD*

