#### Patients with heart disease and diabetes

- Patients with established atherosclerotic heart disease (history of MI, PCI + stent, CABG, angina) or heart failure with LV ejection fraction < 45% are likely to benefit from an SGLT2 inhibitor
  - NICE and local formulary guidance currently restricts prescribing to patients intolerant of other agents
  - Patients with the above heart conditions should nevertheless be referred to diabetes service as inpatients for consideration of switch to SGLT2 inhibitor or to plan for outpatient review to discuss this

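### The statin guidance switches every existing prescription to its listed dose with no exception for a higher current dose, so a patient with angina only could, read literally, be stepped down to atorvastatin 20 mg

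*Protocol*

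**What the plan says.** All the text is in the protocol, mainly in Section S2 (management summaries).

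- **Lipids and coronary artery disease, Rationale and definitions:** "Known CAD is defined as previous myocardial infarction (MI) or coronary revascularisation". Angina is not mentioned.
- **Treatment with statins, opening line:** "Switch any existing statin prescriptions to those recommended below". The checks named there are the ALT level and unexplained muscle pain. The patient's current dose is not considered.
- **Treatment with statins, branches:**
  - "Patients with known CAD should be taking atorvastatin 80mg OD".
  - "Patients without the above, but who have QRISK3" of 10% or more are listed for 20 mg.
  - Patients over 40 with type 1 diabetes, and patients with CKD, "should be offered atorvastatin 20mg OD regardless of QRISK3 score".
  - Patients with QRISK3 below 10% "but with CT calcium score ≥ 1 should be taking atorvastatin 20mg OD".
- **Follow up and referral:** the GP practice repeats the lipid profile at 3-4 months. If non-HDL cholesterol has not dropped by more than 40%, the statin dose is doubled, with a ceiling of atorvastatin 80 mg.
- **Diabetes, Patients with heart disease and diabetes:** "Patients with established atherosclerotic heart disease (history of MI, PCI + stent, CABG, angina") are to be referred for consideration of an SGLT2 inhibitor.
- **Atrial fibrillation, Anticoagulation:** antiplatelet treatment after a vascular event, with MI and stroke as the examples, is classed as secondary prevention.

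The Methods section says the intervention group is treated under standardised protocols. The Cardiovascular treatments section describes the summaries as reflecting current best practice and makes them available online to primary care. The usual care team starts treatment and the GP optimises it.

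**The concern.** A rule that standardises treatment should not lower it by accident. The switch line covers every existing statin prescription, and the listed doses fall into two tiers: 80 mg for known CAD and 20 mg for everyone else who qualifies. Because known CAD is defined narrowly, some patients whom the same appendix regards as having established disease sit in the lower tier. If such a patient arrives on 40 or 80 mg, the literal instruction is to reduce the dose.

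What is at stake is the care of a subset of the intervention arm. The intervention is meant to find and correct undertreated cardiovascular disease, so a line that can reduce existing treatment works against its purpose. The pilot is also meant to lead to a definitive multicentre trial, into which the summaries could be carried.

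**Working it through.** The plan has no figure to reproduce here, so the check is a trace through the text followed by simple dose ratios.

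**Step 1: compare the two lists.** The diabetes summary names four histories: MI, PCI with stent, CABG and angina. Known CAD in the lipid summary covers MI and coronary revascularisation, which takes in the first three. Angina is the one left out.

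**Step 2: trace a patient with angina and no MI or revascularisation.**

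| Condition | Listed atorvastatin dose |
|---|---|
| Known CAD | 80 mg, but this patient does not qualify |
| QRISK3 at or above 10% | 20 mg |
| CKD, or type 1 diabetes and over 40 | 20 mg |
| QRISK3 below 10%, calcium score at least 1 | 20 mg |
| None of these | no statin branch applies |

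The highest listed starting dose this patient can reach is 20 mg. The trace leaves aside the separate pathway for very high cholesterol, which relies on a cited strategy that is not reproduced in the protocol.

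**Step 3: apply the switch line to a patient in one of the 20 mg branches.** With listed dose L and current dose C, the proportional reduction is 1 − L/C.

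- C = 80 mg: 1 − 20/80 = 0.75, a 75% reduction.
- C = 40 mg: 1 − 20/40 = 0.50, a 50% reduction.

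**Step 4: apply the follow-up rule.** One doubling gives 2 × 20 = 40 mg.

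- From an original 40 mg, this restores the dose, but only after 3-4 months and only if the lipid criterion triggers it.
- From an original 80 mg, it reaches 40/80 = half the original dose. A return to 80 mg would need a second doubling, and the section names only the one repeat profile at 3-4 months.

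**Step 5: look for an exception elsewhere.** The Cardiovascular treatments section defers in general terms to local and (inter)national guidelines. It says nothing about angina or about an existing higher dose. Neither the aspirin section nor the follow-up section protects a current dose.

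**Step 6: consider a prior stroke.** A patient with stroke but no MI or revascularisation is also outside known CAD, so the same switch line applies. The atrial fibrillation summary treats stroke as a secondary-prevention event, so the missing exception matters for this patient too.

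**The case against.** The strongest reply is that the two definitions serve different decisions. One triggers high-dose statin and aspirin; the other selects people for a diabetes referral. A referral list may reasonably be wider than a treatment trigger. That stands, so the difference between them is a difference in scope and not, by itself, two contradictory orders.

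Second, a reader might infer that the protocol undertreats angina by listing 20 mg where 80 mg is needed. The documents do not support this. They give a disease label for angina but no statin dose, and the lipid guidance they cite is not reproduced. The same holds for the dose after stroke, and leaving stroke out of a definition of coronary disease is not an error.

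Third, a reader might fault the instruction to calculate QRISK3 in everyone, since the summary says the score "Gives the likelihood of a patient without established cardiovascular disease developing it within the next 10 years". For known CAD the instruction has no effect, because the statin section deals with known CAD first. Restricting the calculation could also leave stroke patients with no branch. It needs no change on this ground.

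Fourth, the switch line could mean only that the agent is standardised to atorvastatin, and clinicians would use judgement. That is plausible and limits the practical effect. But the line points to regimens that each carry a dose, and the text is published for GPs who were not involved in writing it.

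Fifth, the lipid recheck would tend to push the dose back up. If the fall is judged against admission lipids taken on 80 mg, a drop of more than 40% after a step-down is unlikely. This stands as delayed and partial mitigation; it does not prevent the step-down.

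**Conclusion.** The point holds as a minor flaw in the treatment guidance. The statin section orders existing prescriptions to be switched to the listed regimen and does not protect a higher current dose. For a patient with angina only, the listed starting dose is never above 20 mg, so a literal reading cuts 80 mg by 75% or 40 mg by 50%. The general appeal to guidelines and the later doubling soften this but do not remove it.

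The conclusion assumes that the line is applied as written, that the patient has angina without MI or revascularisation and meets one of the 20 mg branches, and that the current dose is above 20 mg. The documents do not say how many such patients there are, and none is assumed. The percentages are dose ratios and say nothing about clinical effect.

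A reader might go further and infer that the trial's results are compromised. They are not on this account. Randomisation is stratified by PEARL score and known cardiovascular disease, not by this definition of CAD. Adequacy of cardiovascular treatment is judged against (inter)national guidance. Sample size, outcomes and analysis are untouched.

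**What to change.** **Main change.** In Treatment with statins, add one sentence after the switch line: an existing higher-intensity statin is not reduced in a patient with established atherosclerotic disease (for example angina, or a prior vascular event of the kind named in the atrial fibrillation summary) unless there is intolerance or a safety reason.

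**Secondary change, for the clinical team to confirm.** In Rationale and definitions, add angina to known CAD so that it matches the diabetes summary. This has consequences beyond wording. It moves angina-only patients to atorvastatin 80 mg, and it puts them under the aspirin 75 mg line for known CAD in Treatment with aspirin, which at present reaches them only through a calcium score of 100 or more.

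**Cost.** One sentence for the main change and a word or two for the secondary one, plus reissue of the online summary. There are no extra tests or visits, and no change to stratification, outcomes or analysis.
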